### Usual care

All participants will receive usual in- or outpatient physical therapy according to the Royal Dutch Guidelines of Physical Therapy [28]. Physical therapy sessions are designed to improve control of standing balance, physical condition, and walking competency. There are no restrictions with respect to content, time, or duration of therapy. Patients randomized to the control group will not have access to the Armed4Stroke telerehabilitation module and no explicit attention is given to the involvement of caregivers in goal-setting and rehabilitation. An 8-week self-reported exercise diary is kept by all the participants to monitor compliance, record fall incidents and telerehabilitation use in a usual care context.

### Outcome measures

#### Primary endpoint

The primary outcome is the mobility domain of the SIS version 3.0 [34], a stroke-specific questionnaire that evaluates self-reported health on 8 domains and a Visual Analogue Scale (VAS). Items are scored on a 5-point Likert scale and domain scores are calculated ranging from 0 to 100 [35]. The SIS has excellent clinimetric properties in English [34, 35] and Dutch [36]. The mobility domain consists of 9 questions about perceived ability to maintain balance, make transfers or walk in the community. The other 7 domains, the VAS and a composite physical domain are evaluated as secondary endpoints.

#### Secondary endpoints patient and caregiver

##### General Self-efficacy Scale (GSES)

The GSES is a valid questionnaire to evaluate general self-efficacy beliefs [37, 38]. The 10 items are rated on a 4-point scale and summed to produce a total score.

##### Preparedness for Caregiving Scale (PCS) and Transition Preparedness Scale (TPS)

The PCS is a reliable and valid tool to assess transition preparedness in caregivers, to assume their new role and to handle the stresses of caregiving [39]. The PCS was translated to Dutch using forward- and back-translations and a modified version was developed to assess transition preparedness in patients, the TPS (Additional file 3: Transition Preparedness Scale). Psychometric evaluation of both scales is currently being conducted by the authors.

##### Hospital Anxiety and Depression Scale (HADS) and Computer Adaptive Tests (CAT)

The HADS is a psychometrically robust measure to assess mood [40, 41]. The scale consists of two 7-item subscales for anxiety and depression. In addition, anxiety and depression items of the Dutch-Flemish PROMIS item bank are administered with CAT [42–44]. CAT dynamically selects the optimal number of questions and the best next question, based on responses to previous questions.

##### Fatigue Severity Scale (FSS)

The 9-item FSS is a reliable and valid instrument to assess fatigue. A mean item score is calculated ranging from 1 to 7 [45].

##### General functioning subscale of the McMaster Family Assessment Device (FAD-GF)

The FAD-GF is a reliable and valid questionnaire to determine general family functioning [46, 47]. A mean item score is calculated ranging from 1 to 4, based on 12 items. Perceptions of family functioning can differ and therefore the FAD-GF is administered to both patients and caregivers [48].

#### Secondary endpoints patient

##### Length of Stay (LOS)

LOS is defined as the number of days between admission and discharge from the rehabilitation centre and will only be considered as a secondary endpoint for patients enrolled during inpatient rehabilitation.

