The Allied Rehabilitation using caregiver MEDiated exercises for Stroke (Armed4Stroke) study investigates a CME program using a blended care approach, in addition to usual care. Compared to previous trials, there is an increased focus on joint goal-setting and rehabilitation in the home situation to increase motivation and stimulate self-management. The training program is developed to achieve important milestones for community ambulation [20, 21] and dyads are supported by a web-based telerehabilitation system with individualized goals, exercise videos and a messaging environment to communicate with their physiotherapist.

The aim of this paper is to describe the Armed4Stroke study design following the SPIRIT Statement (Additional file 1: SPIRIT Checklist). The multicentre, observer-blinded trial aims to assess the effects of the Armed4Stroke program in addition to usual care, starting during the subacute phase poststroke. We hypothesize that the Armed4Stroke program will:Increase patients’ self-reported mobility;Smoothen the care transition, resulting in reduced LOS and better preparedness for discharge;Improve psychological functioning of patients and caregivers, such as mood and self-efficacy.

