### Participants

Seventy-two patients with stroke, and 1 or 2 of their informal caregivers will be enrolled during in- or outpatient rehabilitation. The caregiver can be a partner, family member, or other person close to the patient. They are not healthcare professionals, nor are they paid for their efforts. Stroke is defined by the World Health Organization as “a clinical syndrome typified by rapidly developing signs of focal or global disturbance of cerebral functions, lasting more than 24 hours or leading to death, with no apparent causes other than of vascular origin” [22]. Subarachnoid haemorrhage, and stroke resulting from a brain tumour or traumatic brain injury are excluded as these subtypes differ in their prognosis.

Inclusion criteria for both patient and caregiver are: 1) 18 years or older; 2) written informed consent; 3) able to understand the Dutch language on sufficient level to understand instructions and complete the questionnaires; and 4) motivated for CME. Inclusion criteria for the patient are: 1) < 3 months poststroke; 2) living independently prior to stroke; 3) discharged or planned to be discharged home; 4) able to follow instructions (Montreal Cognitive Assessment [MoCA] score > 21 points); and 5) able and willing to appoint an informal caregiver. An additional inclusion criterion for the caregiver is: being medically stable and able to support the patient. A trained physiotherapist will judge safety and determine if caregivers are physically and mentally able to support the patient during an intake exercise session. Exclusion criteria for both patient and caregiver will be a serious comorbidity that interferes with participation, e.g., premorbid restrictions in mobility as a result of a neurological disease, congestive heart failure or fractures of the lower extremity. Patients will not be enrolled in other clinical trials during the study period.

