### Study procedures

Every patient with stroke, starting in- or outpatient rehabilitation is screened for eligibility according to the inclusion and exclusion criteria by their rehabilitation physician and/or physiotherapist. Eligible dyads receive verbal and written information about the study. If a dyad wants to participate after a reflection period of 1 week, the intake exercise session is scheduled. Upon enrolment, informed consent will be signed by patient and caregiver(s) (Additional file 2: Informed consent form) and primary and secondary endpoints are measured by an independent assessor (MM, CN). Following the assessments, an activity monitor is worn by the patient for 1 week and dyads are randomized to the intervention or control group at a 1:1 ratio using an online randomization module with a minimization algorithm to prevent unequal group sizes. The module will be managed by a researcher (EW, GK) from the initiating institute, not involved in inclusion, assessment or intervention delivery. Factors in the minimization include: 1) centre; 2) inpatient versus outpatient; 3) ≥70 years versus < 70; and 4) Functional Ambulation Category (FAC) 5 versus FAC < 5. Primary and secondary endpoints are repeated by a blinded assessor (MM) at the end of treatment and 6 months follow-up (Fig. 1: Study design). During the study period, serious adverse events will be recorded and reported to the Medical Ethics Review Committee of VU Medical Centre. Data collection is done using electronic Case Report Forms (eCRFs) within the Good Clinical Practice-proof, cloud-based clinical data management platform Castor EDC [27]. The study is monitored by the independent clinical research bureau from VU medical centre. Univariate checks, e.g., range checks, and conditional variables are built-in the eCRFs. The first participant was enrolled on September 2nd 2019 and participants are currently being recruited and enrolled.

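### Length of stay is counted from admission and the stated model omits days from admission to randomisation, which can cost precision but does not bias the comparison

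*Protocol article*

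**What the plan says.** The section on Length of Stay sets the clock: "LOS is defined as the number of days between admission and discharge from the rehabilitation centre". It adds that LOS "will only be considered as a secondary endpoint for patients enrolled during inpatient rehabilitation". The size of that subset is not given.

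Study procedures place randomisation some time after admission. Screening comes at the start of rehabilitation: "Every patient with stroke, starting in- or outpatient rehabilitation is screened for eligibility". Then: "If a dyad wants to participate after a reflection period of 1 week, the intake exercise session is scheduled". Consent and baseline measurements come next, and after them: "Following the assessments, an activity monitor is worn by the patient for 1 week and dyads are randomized to the intervention or control group".

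The minimisation factors are centre, inpatient or outpatient status, age group and Functional Ambulation Category. Under Data analyses, the endpoints go into a linear mixed model with time since stroke, allocation, the minimisation factors and the outcome's baseline value. Days from admission to randomisation appear in neither list.

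The second hypothesis in the Background is: "Smoothen the care transition, resulting in reduced LOS and better preparedness for discharge".

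**The concern.** LOS in this trial is the sum of two intervals. The first, from admission to randomisation, is complete before allocation. The second, from randomisation to discharge, is the only one the programme can shorten. If the first interval varies between patients and is not in the model, its variation can enter the treatment comparison as noise, and a chance difference between arms can shift the estimate.

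Three features make this worth raising.

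- LOS is analysed only in the inpatients among 72 dyads (74 in the abstract), so the comparison is small.
- No other listed endpoint measures when patients go home. The two preparedness scales measure readiness.
- Earlier discharge is prominent in the title and conclusions, and the Background cites an LOS reduction in an earlier Australian trial.

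The article states both the endpoint definition and the covariate list, so the point concerns what is written and not detail left to an analysis plan.

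**Working it through.** **Plan's own figure.** The article gives no SD, effect or sample size for LOS. Its only calculation is for the primary endpoint: 2 × (1.960 + 0.842)² × 14² / 10² = 30.8, or 31 per arm against the stated minimum of 30. That calculation is not affected by this point.

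**Inputs.** From the article: the clock start, the order of procedures, the covariates and the minimisation factors. Assumed, because the article is silent: SD of days before randomisation 7, 14 or 21; SD of days after randomisation 20; correlation ρ between the two; 20 inpatients per arm; a true reduction of 14 days; two-sided alpha 0.05; normal approximation.

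**Step 1: decomposition.** Let A = days from admission to randomisation and R = days from randomisation to discharge. Then LOS = A + R and

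Var(LOS) = SD_A² + SD_R² + 2ρ·SD_A·SD_R.

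**Step 2: share of variance if independent (ρ = 0).** SD_A² / (SD_A² + SD_R²):

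- SD_A 7: 49 / 449 = 11%
- SD_A 14: 196 / 596 = 33%
- SD_A 21: 441 / 841 = 52%

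**Step 3: power without adjustment for A.** Power = Φ(14 / (SD × √(2/20)) − 1.96). Counting from randomisation, SD = 20 and power is 60% at any ρ. Counting from admission (entries for SD_A 7 / 14 / 21):

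| ρ | SD of LOS | Variance relative to R | Power |
|---|---|---|---|
| 0 | 21.2 / 24.4 / 29.0 | 1.12 / 1.49 / 2.10 | 55% / 44% / 33% |
| +0.3 | 23.1 / 27.6 / 33.1 | 1.33 / 1.91 / 2.73 | 48% / 36% / 27% |
| −0.5 | 17.6 / 17.8 / 20.5 | 0.77 / 0.79 / 1.05 | 71% / 70% / 58% |

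The two clocks break even where SD_A² + 2ρ·SD_A·SD_R = 0, that is ρ = −SD_A / (2·SD_R): −0.17 / −0.35 / −0.53. Below that value, counting from admission is the more precise of the two. With SD_R = 25 the pattern is the same: at ρ = 0, power is 43% from randomisation and 40% / 34% / 27% from admission.

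**Step 4: chance imbalance.** The SE of the between-arm difference in mean A is SD_A × √(2/20) = 2.2 / 4.4 / 6.6 days. The probability of a difference of 5 days or more in either direction is about 2% / 26% / 45%. The slope of R on A is β = ρ·SD_R / SD_A, so a 5-day imbalance shifts the expected LOS difference by 5 × (1 + β). At ρ = 0 that is the full 5 days. At ρ = −0.5 and SD_A = 14, β = −0.71 and the shift is 1.4 days.

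**Step 5: adjustment.** Suppose R = a + τ·T + γ·A + e, where T is treatment. Adding A to both sides gives LOS = a + τ·T + (γ + 1)·A + e. The estimate of τ and the residuals are the same for either clock. The residual variance is SD_R²(1 − ρ²). Since

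Var(LOS) = SD_R²(1 − ρ²) + (SD_A + ρ·SD_R)²,

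it cannot exceed Var(LOS), and it cannot exceed SD_R². Adjusted power is 60% at ρ = 0, 64% at ρ = ±0.3 and 72% at ρ = ±0.5. This matches or beats both unadjusted versions in every row, apart from one degree of freedom.

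**The case against.** The case on the other side is strong, and much of it stands.

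- **No bias.** A reader might infer that counting from admission biases the LOS comparison. It does not. Days before randomisation are fixed before allocation and equal in expectation, so the expected difference in days is unchanged. The standard error already allows for chance imbalance.
- **The variance share is not a finding about this trial.** A reader might take about a third of LOS variance as lost. That needs independence and an assumed SD of 14. If total stay is set largely by severity and discharge planning, and enrolment delay by logistics, later randomisation means a shorter remaining stay. For example, with total SD 24.4 independent of A, power is 44% from admission but 41% / 35% / 28% from randomisation for SD_A 7 / 14 / 21.
- **A delay is not variation.** If the reflection week is the same for everyone, it adds no noise. About one week before randomisation is clear from the procedures. A second week depends on whether randomisation follows the monitor week, which the wording leaves open. The three-month limit runs from stroke, not from admission.
- **Partly covered already.** Time since stroke, if taken at enrolment, contains the interval from admission as a component. It also contains the interval from stroke to admission, so it captures the relevant days only in part. LOS has no baseline value to help.
- **The second hypothesis does not rest on LOS alone.** It also names preparedness, which has its own scales for patients and caregivers.
- **Total LOS has a use.** The Discussion lists it among endpoints usable for cost-effectiveness.

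These points defeat any claim that the definition is wrong in itself or must be replaced. They leave the missing covariate: by Step 5, adding it helps or is neutral whatever ρ is.

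**Conclusion.** The point holds in a limited form. LOS includes days that treatment cannot affect, and the stated covariates account for them only in part. The consequence is possible loss of precision and exposure to chance imbalance in one secondary endpoint, analysed in a subset of unstated size. The primary endpoint and its sample size are untouched.

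The size cannot be derived from the documents. Under the assumptions above, with 20 inpatients per arm, a 14-day effect and independent intervals, power falls from 60% to between 55% and 33%. With sufficiently negative correlation the loss disappears or reverses. What does not depend on these assumptions is that a linear model containing days from admission to randomisation does at least as well as either unadjusted version, less one degree of freedom. The equality of the two clocks is exact only for a linear model on the scale of days, which is the type of model the article states.

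**What to change.** Prespecify days from admission to randomisation as a covariate in the LOS analysis, in addition to the covariates already listed. The admission-to-discharge definition can then stay, because the treatment estimate is the same for either clock. Report days from randomisation to discharge by arm as the part that treatment can change, and keep total LOS for description and for later cost work.

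The cost is one degree of freedom in a small subset and a dated amendment. The article reports 26 participants enrolled and recruitment continuing, so the change can be made before analysis; it should be made without sight of outcomes by arm. Admission and discharge dates are needed for LOS in any case. The randomisation date should be available from the online module, although the article does not say so explicitly.

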##### Stroke Self-efficacy Questionnaire (SSEQ)

The SSEQ is a reliable and valid measure of self-efficacy in relevant domains of functioning poststroke [49]. The SSEQ consists of 13 items with scores ranging from 0 to 10. Rasch analysis identified 2 dimensions: 1) Activity; and 2) Self-management [50]; and we will report these separate dimensions.

##### RMI

The RMI measures self-reported mobility poststroke with 14 questions and 1 observation [51]. A total score of 0 to 15 is calculated. Psychometric properties of the English and Dutch version [51–53] have been established.

##### FAC score

Functional walking ability is evaluated with the 0 to 5 FAC score, a reliable, valid and responsive scale poststroke [54]. An assessor rates the level of independence, regardless of the use of assistive devices.

##### Six-minute Walking Test (6MWT) and Five-meter Walk Test (5MWT)

The 6MWT [55, 56] and 5MWT [57, 58] are psychometrically robust tests to determine walking capacity poststroke. Distance walked during 6 min is recorded in meters. Mean gait speed is calculated in meters per second based on 3 repetitions. The 5MWT at a comfortable speed is recommended as the most responsive and convenient method of evaluating gait speed, when compared to fast speed or a 10-m distance [59].

##### Leg section of the Motricity Index (MI-leg)

The MI-leg is a reliable and valid tool to assess strength and range of motion of the paretic leg [60, 61]. The test consists of 3 joint movements, i.e., ankle dorsiflexion, knee extension, and hip flexion which are rated on a 0 to 33 scale and summed. When the maximum score of 99 is achieved, 1 point is added.

##### Berg Balance Scale (BBS)

The BBS measures balance during 14 tasks [62]. Items are rated on a 0 to 4 scale and a total score is calculated ranging from 0 to 56. Reliability, validity and responsiveness are established poststroke [62, 63].

##### MOX-2 activity monitor

Physical activity will be measured for 7 days during wake hours using the MOX-2. The MOX-2 is a small, lightweight device and will be worn on the non-paretic thigh using an adhesive plaster. It measures 3D-accelerations during daily activities and mean daily physical activity is calculated over 1 week.

##### Nottingham Extended Activities of Daily Living index (NEADL)

The NEADL is a 22-item reliable and valid test of extended ADL poststroke [30, 64, 65]. Rasch analysis did not support a unidimensional structure or polytomous scoring [65]. Therefore, the original dichotomous scoring method and domain scores: 1) Mobility; 2) Kitchen; 3) Household; and 4) Leisure will be used.

##### Community Ambulation Questionnaire (CAQ)

The CAQ measures the level of independent walking outside the home, i.e., without physical assistance or supervision [66]. Patients are categorized as: 1) Unable to walk outside unassisted; 2) Only ambulant around the house (e.g., as far as the letterbox); 3) Ambulant in the immediate environment (e.g., around the block); or 4) Independent community ambulation (e.g., to visit a friend or shop).

##### The EuroQol 5D (EQ-5D)

The 3-level version of the EQ-5D is a valid and reliable, generic measure of health-related quality of life poststroke [67, 68]. The instrument consists of 5 dimensions: 1) Mobility; 2) Self-care; 3) Usual activities; 4) Pain/Discomfort; and 5) Anxiety/Depression; and a VAS to assess perceived health.

##### Modified Rankin Scale (mRS)

The mRS is a widely used 0 to 5 global rating scale of disability poststroke. An assessor rates the level of independence in pre-stroke activities. The scale has good reliability and validity poststroke [69].

#### Secondary endpoints caregiver

##### Caregiver Strain Index (CSI) and Care-related Quality of Life instrument (CarerQoL)

Both the CSI [70–72] and the CarerQoL [73–75] are reliable and valid instruments to evaluate caregiver burden. The CSI consists of 13 items which are summed to produce a total score. The CarerQoL consists of seven 3-level burden dimensions and a 0 to 100 VAS measuring happiness.

### Power analysis

We expect a significant improvement of 10 points (10%) on the SIS mobility domain (mean 79.4, SD 14) in favour of the intervention group. We expect that minimally 30 patients are required per trial arm [76]. Including 20% drop-outs (for patients and caregivers), a sample size of 72 patient-caregiver dyads is needed to achieve sufficient statistical power of 80% using a two-tailed significance level alpha of *p* < 0.05. Currently, 26 participants have been enrolled in the ongoing trial.

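### 72 dyads do not give the stated 80% power after 20% drop-out: the loss was added rather than divided out and 30 per arm is slightly too few, so power is about 76%

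*Protocol article*

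**What the plan says.** The calculation is in the protocol article, Methods, Power analysis. The target difference and its variability are given as "10 points (10%) on the SIS mobility domain (mean 79.4, SD 14"). The base requirement follows, with a literature citation: "We expect that minimally 30 patients are required per trial arm". The total is then stated: "Including 20% drop-outs (for patients and caregivers), a sample size of 72 patient-caregiver dyads is needed to achieve sufficient statistical power of 80"%, at a two-tailed alpha of 0.05.

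The Design section gives 1:1 allocation. The Participants section repeats 72 patients, whereas the abstract gives 74 dyads. The Data analyses section plans a linear mixed model that includes the baseline value of the outcome, time since stroke and the minimization factors. The Power analysis section uses no baseline correlation and does not name the test behind the calculation.

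**The concern.** All the inputs and the result are printed in one short paragraph, so the claim can be checked without outside information. Two steps look wrong, and both err in the same direction. The drop-out allowance appears to add 20% to the required number instead of dividing by the proportion retained. The base of 30 per arm also appears slightly too small for the stated difference, SD, alpha and power.

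This is the article's only power statement for the primary endpoint, and it justifies the enrolment target. The background describes two earlier trials of this approach as neutral on self-reported mobility, and the conclusion presents this trial as a step towards a larger one. If this trial is also neutral, readers will weigh that result against a claimed 80% power that the stated calculation does not support.

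**Working it through.** **Inputs** (Power analysis section, with 1:1 allocation from the Design section): difference 10, SD 14, two-sided alpha 0.05, power 80%, 30 per arm, drop-out 20%, total 72. The standardised difference is d = 10/14 = 0.714.

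**1. Reproducing 72.** 2 x 30 = 60, and 60 x 1.20 = 72 exactly. The printed total therefore matches multiplication by 1 + 0.20.

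**2. Correct allowance for loss.** To retain N after a loss of 20%, enrol N/(1 - 0.20). Here 60/0.80 = 75, or 76 for equal arms. In the other direction, 72 x 0.80 = 57.6 dyads, or 28.8 per arm, which is below 30. Enrolling 72 retains 60 only if the loss is at most 1 - 60/72 = 16.7%. This step depends on no power formula.

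**3. Base number per arm.**
- Normal approximation: n = 2(1.960 + 0.842)^2 / 0.714^2 = 30.8, so 31.
- Two-sample t-test (noncentral t): 31.8, so 32.

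**4. Power.** The normal approximation is power = Phi(d x sqrt(n/2) - 1.960). For n = 28.8 this is Phi(2.711 - 1.960) = 77.4%. The t-test values come from the noncentral t distribution.

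| Evaluable per arm | Normal approximation | t-test |
|---|---|---|
| 28.8 (72 enrolled, 20% lost) | 77.4% | 75.9% |
| 29 | 77.6% | 76.2% |
| 29.6 (74 enrolled, 20% lost) | 78.5% | 77.1% |
| 30 | 79.0% | 77.6% |
| 31 | 80.3% | 79.0% |
| 32 | 81.5% | 80.3% |

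The abstract's 74 dyads do not restore 80% either.

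**5. Detectable difference with 80% power at 28.8 per arm.** 10.5 points by the t-test. By the normal approximation it is 2.802 x 14 x sqrt(2/28.8) = 10.3 points.

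**6. Enrolment needed for 80% power in an unadjusted comparison.** Normal approximation: 62/0.80 = 77.5, so 78. t-test: 64/0.80 = 80.

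**7. Effect of baseline adjustment.** If SD 14 is the unadjusted SD, adjustment reduces it to 14 x sqrt(1 - r^2), where r is the baseline-outcome correlation. The article gives no r, so these values are assumptions. At 28.8 per arm, t-test power is 77.6% for r = 0.2, 79.7% for 0.3, 82.8% for 0.4 and 86.8% for 0.5. It reaches 80% at r of about 0.31 (about 0.25 by the normal approximation).

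**The case against.** The strongest reply is that the endpoints will not be analysed with an unadjusted t-test. The planned mixed model adjusts for baseline, and a correlation of only about 0.31 is enough to recover 80%. The model can also use data from dyads seen at the end of treatment but lost before the 6-month visit, so 57.6 may understate the information available. This stands as a limit on the finding: the documents do not show that the final analysis will be underpowered. It does not rescue the printed statement, which invokes no correlation and no gain from repeated measures.

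A second reply is that the base of 30 is nearly right. By the normal approximation it is short by less than one patient per arm and gives 79.0%, and the figure is attributed to a cited source. This is fair. The base is the smaller of the two faults, and only the t-test puts it more than two points below 80%. The citation cannot justify the drop-out step, which fails by simple division.

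A third reply is that 3 to 4 points of power matter little in a phase II trial whose 20% drop-out is itself a planning guess. The size is indeed modest. The statement is still incorrect on its own inputs, and correcting it costs almost nothing.

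**Conclusion.** The power statement is wrong as written. On its own inputs, 72 dyads with 20% loss leave about 58 evaluable, fewer than the 60 that the same paragraph requires. Power for 10 points is then about 76% by the two-sample t-test, or 77% by the normal approximation, and the difference detectable with 80% power is about 10.5 points. The drop-out step is the main error and holds under any formula; the base of 30 per arm adds a smaller shortfall.

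The power figures assume an unadjusted two-arm comparison, SD 14 as the between-patient SD, equal arms and exactly 20% loss. They concern the calculation as stated. The baseline-adjusted model may reach 80% or more, but the article gives no correlation from which to show it.

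**What to change.** Keep the number enrolled and correct the statement, for example: 72 dyads, 20% drop-out, about 58 evaluable, giving about 76% power to detect 10 points with SD 14 (two-sample t-test, two-sided 0.05). Remove the implication that 72 preserves 30 per arm after 20% loss, and note that this would take 60/0.80 = 75 dyads. Use one enrolment total in the abstract, Participants and Power analysis sections.

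A claim of 80% power for the baseline-adjusted model is possible only if the assumed correlation (at least about 0.31) is written down and supported. Choosing it afterwards to reach 80% would be weak, particularly as the article reports 26 participants already enrolled.

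The cost is a change of wording and a slightly less favourable power figure. No extra patients are needed, and the design and analysis do not change.
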